### Statistical methods and analysis

Descriptive data will be reported as the mean and SD for continuous variables and frequency statistics for non-continuous variables. Prior to statistical analysis, normality tests will establish data distribution; if data are non-normally distributed, transformation and the use of non-parametric statistical analysis tests will be employed. All tests will be two-sided, and alpha significant will be set a priori p<0.05. A between-subjects and within-subjects ANOVA will be used to assess the effect of the intervention on all outcome variables. Any statistically significant two-way interactions will be followed up using post hoc analysis with Bonferroni corrections to account for multiple comparisons. The magnitude of any differences will be presented using 95% CI and Cohen’s D for effect size.

Supporting analysis of the primary outcome will include a per-protocol analysis including patients with compliance >80% to intervention. In addition to the primary adjusted analysis, the unadjusted mean differences between groups will be reported using t-test, reporting 95% CI. Study participant flow will be recorded and reported as per CONSORT guidelines. Analysis will be conducted on a pairwise case basis. Therefore, all missing data will be reported, and patterns investigated. Sensitivity analysis will be conducted using multiple imputation techniques to assess the effect of missing data on primary outcomes. Post-intervention adverse events between groups will be analysed using Fisher’s exact test. All analysis will be conducted using SPSS.

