### Sample size calculation

For both phases, the sample size calculation was based on the effect size for a significant and clinically meaningful reduction in patient-reported pain (ie, the primary outcome measure, the Brief Pain Inventory (BPI))^54^ and calculated using G Power V.3.1.9.6.

Phase One: using a repeated measures analysis of variance (ANOVA; between factors) sample size calculation with an effect size of d=0.64,^54^ power=0.95, alpha=0.05, considering two treatment arms and three measurements timepoints (ie, pre-intervention and post-intervention, and follow-up), the required sample size is 24 patients. However, to account for a 10% drop out (as guided by previous ADMR publications^50 55 56^), a minimum of 28 patients will be recruited (n=14 per study arm).

Phase Two: using a repeated measures ANOVA (between factors) sample size calculation with an effect size of d=0.64,^54^ power=0.95, alpha=0.05, two treatment arms, and four measurements timepoints (ie, pre-intervention, end-week 1 intervention, end-week 2 intervention and post-intervention), the required sample size is 22 patients. However, to account for a 10% drop-out, 26 patients will be recruited (n=13 per study arm).

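### A normality pre-test is allowed to choose the primary BPI analysis at 11 to 14 patients per arm, and the fallback leaves the test and the estimand undetermined

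*Protocol article*

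**What the plan says.** All of the following is in the protocol article, Statistical methods and analysis, unless another section is named.

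- The gate: "Prior to statistical analysis, normality tests will establish data distribution".
- What follows a failure: "if data are non-normally distributed, transformation and the use of non-parametric statistical analysis tests will be employed". No order is given between transformation and non-parametric testing, and no non-parametric test is named.
- The default: "A between-subjects and within-subjects ANOVA will be used to assess the effect of the intervention on all outcome variables". The primary outcome is not exempt from the gate.
- Follow-up: "Any statistically significant two-way interactions will be followed up using post hoc analysis with Bonferroni corrections".
- Reporting: "The magnitude of any differences will be presented using 95% CI and" Cohen's d. Unadjusted mean differences by t-test, with 95% CI, are promised alongside the primary analysis.
- Level: "All tests will be two-sided, and alpha significant will be set a priori p<0.05". Whether this level also governs the normality tests is not said.

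The Phase One section on patient-reported outcome measures gives a 2-point BPI reduction as the minimally clinically important difference. The Phase Two section on the experimental intervention chooses the BFR pressure in steps. BPI comes first, the Lower Extremity Function Scale (LEFS) comes next if the BPI difference is not statistically significant, and a default applies if neither outcome separates the arms.

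**The concern.** A normality test at this sample size is a poor guide to whether ANOVA is safe. It has little power against departures that matter, and it rejects at its nominal rate, or more often over several tests, when nothing is wrong. Using it to select the primary analysis makes the test and the estimand depend on a noisy preliminary result.

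The fallback also does not fit the rest of the plan. The plan relies on a two-way interaction, confidence intervals and Cohen's d. The common rank tests on raw scores (Mann-Whitney between arms, Friedman within arm) do not test that interaction and do not yield those estimates. A transformed BPI is no longer on the scale of the 2-point threshold.

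The stakes are highest in Phase One. Whether the pressure decision stops at BPI or passes to LEFS depends on a significance verdict, and the pre-test decides which procedure delivers that verdict.

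**Working it through.** **1. Patients per arm.** The sample size section states for Phase One "effect size of d=0.64,^54^ power=0.95, alpha=0.05, considering two treatment arms and three measurements timepoints", and "a minimum of 28 patients will be recruited (n=14 per study arm"). I used the noncentral F for the between factor, with λ = f²·N·m / [1 + (m − 1)ρ], df 1 and N − 2, and an assumed ρ = 0.5.

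- Phase One: 0.64² × 24 × 3 / 2 = 14.75; power 0.956, so N = 24.
- Phase Two: 0.64² × 22 × 4 / 2.5 = 14.42; power 0.950, so N = 22.
- Dropout: 24/0.9 = 26.7, so 27, and 28 as an even total. 22/0.9 = 24.4, so 25, and 26 as an even total.

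The plan's figures reproduce, with 0.64 entered as Cohen's f; the d label is a separate matter. Patients per arm are 12-14 in Phase One and 11-13 in Phase Two. Arm-by-time cells number 2 × 3 = 6 and 2 × 4 = 8.

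**2. How often exactly normal data would trigger the switch.** I assumed Shapiro-Wilk at 5%, with one failure enough to trigger. If the cells were independent, the rate would be 1 − 0.95⁶ = 26.5% and 1 − 0.95⁸ = 33.7%. Simulation with correlated normal data (4,000 runs per setting, correlation 0.5, 0.7 and 0.9) gave:

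| Quantity tested | Phase One | Phase Two |
|---|---|---|
| Every arm-by-time cell | 21-27% | 25-34% |
| Each timepoint, arms pooled | 11-15% | 14-18% |
| Change score in each arm | 9-10% | 9-10% |
| Residuals (one test) | 3-6% | 4-6% |

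A separate run put the pooled-timepoint reading at 13-19%, so its overall range is 11-19%.

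**3. Discrete scores.** For a single 0-10 integer item (mean 4.5, SD 2 and correlation 0.5, all assumed), the switch fires in about 50-62% of trials with cells, 40-51% with pooled timepoints, 22-24% with change scores per arm and 9-11% with pooled change residuals. For a score in steps of a quarter point, as from a four-item mean, the cell-wise rates are 24% and 32%, about the same as for continuous data. The excess is therefore specific to a coarse item.

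**4. What the switch costs.** A two-stage procedure was simulated on normal data (6,000 runs, correlation 0.5). It used a t-test on change, replaced by Mann-Whitney on change if any cell failed.

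| | t-test always | Two-stage |
|---|---|---|
| Type I error, Phase One / Two | 0.054 / 0.051 | 0.053 / 0.048 |
| Power, d = 0.64 | 0.372 / 0.352 | 0.365 / 0.341 |
| Power, d = 1.28 (f = 0.64) | 0.904 / 0.886 | 0.896 / 0.878 |

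The loss is about 1 point of power, and false positives are not inflated.

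Like for like, with 13 per arm and ranks used every time:

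- d = 0.64, correlation 0.5: change score, 0.34 against 0.30; ANCOVA against rank ANCOVA, 0.41 against 0.38.
- d = 0.64, correlation 0.7: end score, 0.35 against 0.32; ANCOVA against rank ANCOVA, 0.56 against 0.51.
- d = 1.28, correlation 0.5: end score, 0.87 against 0.84; ANCOVA against rank ANCOVA, 0.94 against 0.92.

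These pairs differ by 2 to 5 points. Other runs put the cost at about 3 to 8.

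**5. What baseline adjustment adds.** At 13 per arm and d = 0.64, an end-score t-test has power of about 0.35. Baseline-adjusted ANCOVA has about 0.41-0.44 at correlation 0.5 and 0.56-0.59 at correlation 0.7.

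**The case against.** The strongest reply is that this is condensed article wording. An analysis plan that is not shown may name the normality test, apply it to residuals and name a fallback that tests differential change. That reply limits the point but does not remove it, because the article states a selection rule and does not merely omit detail.

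Three stronger readings are tempting, and the documents do not support them.

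- *A quarter to a third of trials with normal data would be switched.* That holds only if every arm-by-time cell is tested and one failure is enough. The article specifies neither, and other readings give 3% to 19%. The wording refers to the data, but it does not exclude residuals.
- *The fallback cannot assess the group-by-time effect.* No test is named. Transformation is also listed, and ANOVA on a transformed score keeps its interaction. A rank test on change scores addresses the group difference in change, and rank ANCOVA adjusts for baseline. What can be said is that the fallback is not stated to test group-by-time.
- *The rule costs a large amount of power.* Setting Mann-Whitney on the end score (0.30) against ANCOVA (0.57) at d = 0.64 and correlation 0.7 changes two things at once. Most of that gap comes from baseline adjustment, which is a gain from the proposed fix and not a cost of the pre-test.

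It is also fair that the separately promised t-test keeps a mean difference with 95% CI on the BPI scale. That protects reporting. It does not settle which test is primary when a rank test and the t-test disagree.

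**Conclusion.** The point stands as a specification fault that should be corrected. The plan makes the primary BPI test depend on an unspecified pre-test at 11-14 patients per arm, and its fallback does not fit the plan's own interaction follow-up, effect measures and threshold. On normal data the false-trigger rate lies between about 3% and 34%, depending on choices the article does not make. A single integer item would trigger more often under the same readings, from about 9-11% (pooled change residuals) to 50-62% (cells). These rates assume Shapiro-Wilk at 5% and, for the integer item, a mean of 4.5 and SD of 2.

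The damage is not inflated type I error, and the power cost of ranks is modest. It is that the primary test and estimand are not fixed before the data are seen, in a trial whose first phase feeds a significance verdict into the pressure decision for the second.

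**What to change.** Delete the normality pre-test rule for the primary outcome. State one primary analysis in advance: a linear or mixed model of BPI on its original scale, adjusted for baseline BPI, reporting the between-arm mean difference with 95% CI. Inspect residuals as a diagnostic that does not change the primary analysis. Report a bootstrap or permutation interval as a sensitivity analysis whatever any normality test shows. Have the Phase One pressure decision refer to this model by name, and fix the LEFS analysis in the same way because the second step uses it.

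The cost is a change of wording and slightly more analysis work. No further patients or measurements are needed, and the baseline adjustment should gain power by the amounts shown in the working.

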### Randomisation and blinding procedure

For both phases, a permuted block randomisation method with a 1:1 ratio will be used using random block sizes. Randomisation will be stratified by age (18–36, 37–55 years old) and sex, to prevent an imbalance between groups.^53^ A plain language statement will inform participants that they have an equal chance of receiving low-load RT with either high-pressure or low-pressure BFR (Phase One), or low-load RT with BFR or standard rehabilitation (Phase Two). A sealed envelope will be opened to reveal group allocation by an independent administrator not involved in the recruitment, treatment or assessment of study outcomes. Given the nature of BFR, it is not feasible to blind participants to their treatment allocation. The clinical staff who deliver the study interventions and collect outcome data for the RCT must also be, by necessity, unblinded.

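### The primary BPI analysis is called adjusted, but the only model described is a mixed ANOVA with no covariate; a baseline- and strata-adjusted model would be more efficient

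*Protocol article*

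**What the plan says.** Under Statistical methods and analysis, the model is stated once: "A between-subjects and within-subjects ANOVA will be used to assess the effect of the intervention on all outcome variables". The Brief Pain Inventory (BPI) is the primary outcome, so this covers it. The route to between-arm comparisons is the interaction: "Any statistically significant two-way interactions will be followed up using post hoc analysis with Bonferroni corrections". The following paragraph then says: "In addition to the primary adjusted analysis, the unadjusted mean differences between groups will be reported using t-test, reporting 95% CI". It does not say what the primary analysis is adjusted for.

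Under Sample size calculation, both phases are sized with a repeated measures ANOVA for the between-group factor. The pre-intervention value is one of the repeated measurements in Phase One, "three measurements timepoints (ie, pre-intervention and post-intervention, and follow-up), the required sample size is 24 patients", and in Phase Two, "four measurements timepoints (ie, pre-intervention, end-week 1 intervention, end-week 2 intervention and post-intervention), the required sample size is 22 patients".

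Under Randomisation and blinding procedure: "Randomisation will be stratified by age (18–36, 37–55 years old) and sex, to prevent an imbalance between groups". Neither factor reappears in the analysis text.

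**The concern.** Three things do not fit together.

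- **The label and the model disagree.** A plain between/within ANOVA is not an adjusted analysis in the sense that contrasts with an unadjusted t-test.
- **The sized term is diluted.** Baseline is counted as a level of the time factor, so the group main effect averages in a visit at which treatment cannot have acted. The interaction escapes this, but it spreads the treatment effect over two or three degrees of freedom. The follow-up comparisons also depend on its being significant.
- **The strata are used in the design and left out of the stated model.** Standard errors then tend to be too large.

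These samples are small. With 12 or 11 completers per arm, the chance difference in baseline means has a standard deviation of √(2/12)=0.41 or √(2/11)=0.43 outcome SDs, against a target of 0.64. The Phase One BPI result also feeds the rule for choosing the Phase Two pressure (Phase Two, Experimental intervention), and that rule turns on statistical significance.

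**Working it through.** **Inputs from the documents.** N=24 with m=3 timepoints (Phase One); N=22 with m=4 (Phase Two); effect 0.64; power 0.95; two-sided alpha 0.05; 1:1 allocation. The correlation ρ between timepoints is not given. I take 0.5, with a range of 0.3 to 0.8, under compound symmetry.

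**Step 1. Reproduce the stated sample sizes.** For the between factor, λ = f²Nm/[1+(m−1)ρ], with df 1 and N−2.

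- Phase One: 0.64²×24×3/(1+2×0.5) = 14.75, power 95.6%.
- Phase Two: 0.64²×22×4/(1+3×0.5) = 14.42, power 95.0%.

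Both N reproduce, which confirms that the sized term is the group main effect. They reproduce only with 0.64 entered as Cohen's f, which corresponds to d=1.28. Read as d=0.64 (f=0.32), power would be 45% and 44%. That is a separate matter; here it means showing both effect sizes.

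**Step 2. Power of each candidate test.** Assume no true baseline difference and a constant difference d at every post-baseline visit; let q=m−1.

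- Main effect: λ = (N/4)[d(m−1)/m]² / {[1+(m−1)ρ]/m}, df 1, N−2.
- Interaction: λ = (N/4)d²[(m−1)/m]/(1−ρ), df m−1, (m−1)(N−2).
- ANCOVA, one visit: λ = (N/4)d²/(1−ρ²), df 1, N−3.
- ANCOVA, post-baseline mean: λ = (N/4)d²/{[1+(q−1)ρ]/q − ρ²}, df 1, N−3.

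At d=0.64 and ρ=0.5:

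- Phase One: 6×0.427²/0.667 = 1.64; 6×0.4096×0.667/0.5 = 3.28; 6×0.4096/0.75 = 3.28; 6×0.4096/0.5 = 4.92.
- Phase Two: 5.5×0.48²/0.625 = 2.03; 5.5×0.4096×0.75/0.5 = 3.38; 5.5×0.4096/0.75 = 3.00; 5.5×0.4096/0.4167 = 5.41.

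| Power, d=0.64 | Main effect | Interaction | ANCOVA, one visit | ANCOVA, post-baseline mean |
|---|---|---|---|---|
| Phase One, ρ=0.3 | 28% | 24% | 35% | 52% |
| Phase One, ρ=0.5 | 23% | 33% | 41% | 56% |
| Phase One, ρ=0.7 | 20% | 51% | 55% | 70% |
| Phase One, ρ=0.8 | 19% | 70% | 70% | 83% |
| Phase Two, ρ=0.3 | 34% | 21% | 32% | 57% |
| Phase Two, ρ=0.5 | 27% | 29% | 38% | 60% |
| Phase Two, ρ=0.7 | 23% | 46% | 51% | 73% |
| Phase Two, ρ=0.8 | 21% | 65% | 66% | 85% |

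The planned unadjusted t-test at one visit has 32% (Phase One) and 30% (Phase Two) power.

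With d=1.28 and ρ=0.5, the four columns are 69%, 89%, 93% and 99% in Phase One, and 77%, 86%, 91% and 99% in Phase Two.

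**Step 3. Other effect patterns (d=0.64, ρ=0.5).** If the effect grows linearly to the last visit, the interaction has 25% and 22%, against 41% and 38% for last-visit ANCOVA. If the effect is present at the last visit only, the interaction has 33% and 29% against the same 41% and 38%. In Phase One the post-baseline mean then carries half the effect, so its λ falls to 4.92/4 = 1.23, below the single-visit 3.28.

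**Step 4. Leaving out the strata.** This was simulated with N=24, one outcome, stratified permuted blocks, 8000 runs, an effect of 1.28 SD for power, and an assumed share R² of outcome variance due to age band and sex.

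- R²=0.1: unadjusted type I error 3.9%; power 86% unadjusted against 88% adjusted.
- R²=0.3: 2.2%; 88% against 94%.

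**Step 5. Cost of the two strata covariates.** Residual df fall from N−3 to N−5. At d=0.64 and ρ=0.5, post-baseline-mean power goes from 56.2% to 55.7% and from 59.7% to 59.2%.

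**The case against.** The strongest reply is that a repeated measures ANOVA with a pre-intervention level is a valid analysis. Its interaction tests differential change from baseline, and the plan follows up interactions, so the low main-effect figures do not describe how the plan would detect an effect. This largely stands. It would be wrong to infer that the planned model ignores baseline. The main effect remains relevant because it is the term on which the trial was sized.

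Second, a reader might infer that no adjusted analysis exists. The documents do not support that: the word may point to covariates listed in a full plan that is not shown, and an article may leave such a list out. What remains is the conflict in the published text between a plain ANOVA and the label.

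Third, a reader might attach the gain to 56% or 60% to any ANCOVA. It belongs to the post-baseline mean only. At a single visit the gain over the interaction is 8 to 9 points at correlation 0.5, 4 to 5 at 0.7 and about none at 0.8. At 0.3 in Phase Two the main effect even slightly exceeds single-visit ANCOVA (34% against 32%).

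Fourth, omitting the strata neither biases the estimate nor inflates type I error, and the documents do not say how strongly age or sex predicts BPI.

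Finally, BPI at T0 is stated for Phase Two. The Phase One text says only that there is a pre-intervention measurement and leaves the schedule to a supplement. That baseline is an outcome level also comes from the sample size section, not from the analysis section.

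**Conclusion.** The point holds as an internal conflict and an avoidable loss of efficiency. The text names an ANOVA without covariates, calls the primary analysis adjusted, sizes the trial on a term that includes the pre-treatment visit, and leaves the randomisation strata out of the stated model.

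Over correlations of 0.3 to 0.8, with compound symmetry and a constant d=0.64 after baseline, baseline-adjusted ANCOVA on the post-baseline mean has more power than either ANOVA test throughout. It reaches 52–83% in Phase One, against 19–28% for the main effect and 24–70% for the interaction. In Phase Two it reaches 57–85%, against 21–34% and 21–65%. Single-visit ANCOVA has 35–70% and 32–66%, a modest gain over the interaction that vanishes at high correlation. These sizes depend on an unstated correlation and an assumed effect pattern.

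The planned analysis should not be read as biased or invalid; omitting the strata only makes it conservative. The change should be made, but it is an efficiency gain and not a condition for a valid trial.

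**What to change.** Make the primary BPI analysis an ANCOVA, or a linear mixed model of post-baseline BPI with visit and treatment-by-visit terms. Use pre-intervention BPI, age band and sex as covariates, and state which visit supplies the pre-intervention value in each phase.

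Name one primary contrast in advance: either the end-of-intervention visit (day 5 in Phase One, day 15 in Phase Two) or the mean of the post-baseline visits. These answer different questions. The mean gains most if the effect is sustained and loses if it appears late. Report the adjusted between-arm difference with its 95% CI whether or not an interaction is significant. Keep the t-test as the unadjusted companion, so that the word adjusted has a defined meaning.

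The cost is revised analysis wording and different SPSS syntax, plus two or three degrees of freedom. The two strata covariates cost under about 1 point of power. No extra patients or visits are needed: pre-intervention BPI is already one of the planned measurements, and age and sex are needed for randomisation.

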### Phase Two RCT

A 3-week RCT (resembling actual inpatient rehabilitation duration at DMRC) will compare the efficacy of the most clinically acceptable BFR pressure from Phase One to standard/conventional UK Defence Rehabilitation residential rehabilitation practice on physiological mechanisms underpinning changes in pain modulation and rehabilitation outcomes. It is hypothesised that the BFR-RT group will have greater reductions in pain, and increases in function, when compared with usual care alone.

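### No single BPI contrast is named as the primary test, and the ANOVA reaches visit-level arm comparisons only through a significant interaction followed by Bonferroni, a route with less power than one planned baseline-adjusted contrast

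*Protocol article*

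**What the plan says.** The section on statistical methods applies a between- and within-subjects ANOVA to every outcome, with "All tests will be two-sided, and alpha significant will be set a priori p<0.05". The next step is "Any statistically significant two-way interactions will be followed up using post hoc analysis with Bonferroni corrections to account for multiple comparisons". The comparisons that make up the Bonferroni family are not listed. The BPI is the primary outcome, but no visit and no contrast is singled out as its primary test.

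The same section also reports the unadjusted between-group mean difference by t-test with a 95% CI. It presents this as an addition to a primary analysis that it calls adjusted.

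The Phase Two hypothesis is that "the BFR-RT group will have greater reductions in pain, and increases in function, when compared with usual care alone". The modelled visits are given under the sample size: in Phase One "three measurements timepoints (ie, pre-intervention and post-intervention, and follow-up"), and in Phase Two "four measurements timepoints (ie, pre-intervention, end-week 1 intervention, end-week 2 intervention and post-intervention"). Phase Two was sized "using a repeated measures ANOVA (between factors) sample size calculation with an effect size of d=0.64", that is, on the arm effect averaged over visits, and Phase One in the same way.

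Under the Phase Two experimental intervention, the BFR pressure is chosen first on BPI. The choice passes to the LEFS if the pain difference is not statistically significant. That step does not say which test is meant.

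**The concern.** The hypothesis about pain can be answered by one comparison: the arms at end of treatment, allowing for where patients started. One planned comparison holds the 5% level with neither an omnibus gate nor a multiplicity correction. Within the primary ANOVA, that comparison must first wait for a significant group-by-time interaction and then meet a stricter threshold. If the family is the modelled visits, the threshold is 0.05/3 = 0.0167 in Phase One and 0.05/4 = 0.0125 in Phase Two. Such a family includes the pre-intervention visit, where randomised arms have no true difference.

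Two things are at stake. A real end-of-treatment difference may be reported as non-significant because of the route taken. And because no primary contrast is named, the arm effect, the interaction, a post hoc comparison and the t-test could each be taken as the BPI result. The rule that picks the Phase Two pressure depends on which one is used.

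**Working it through.** **Inputs.** From the protocol: alpha 0.05 two-sided; d = 0.64; 3 and 4 visits; 24 and 22 patients required, hence n = 12 and 11 per arm. Assumed, because not stated: equal correlation ρ between visits (0.5, varied from 0.3 to 0.8), SD 1, no difference at baseline, an effect equal at both Phase One post-baseline visits, and an effect growing linearly in Phase Two.

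**Step 1: the plan's own figure.** For the between-factors effect, λ = f²·N·m / (1 + (m−1)ρ), with 1 and N−2 df.
- Phase One, f = 0.64: 0.4096 × 24 × 3 / 2 = 14.75, power 0.956.
- Phase Two, f = 0.64: 0.4096 × 22 × 4 / 2.5 = 14.42, power 0.950.

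The stated 24 and 22 are thus reproduced when 0.64 is entered as Cohen's f with ρ = 0.5. For two arms d = 2f, so this corresponds to d = 1.28. With d = 0.64 (f = 0.32), power at these sizes is 45% and 44%. Both effects are carried through below.

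**Step 2: interaction alone.** λ = n·Σ(δⱼ − δ̄)² / (2(1−ρ)), with m−1 and (m−1)(2n−2) df.
- Phase One, δ = 0, 0.64, 0.64: Σ = 0.273; λ = 12 × 0.273 / 1 = 3.28 on 2 and 44 df; power 33%.
- Phase Two, δ = 0, 0.213, 0.427, 0.64: Σ = 0.228; λ = 11 × 0.228 / 1 = 2.50 on 3 and 60 df; power 22%.
- At 1.28, λ is four times as large (13.1 and 10.0): 89% and 73%.

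**Step 3: one contrast at the last visit.**
- Unadjusted t-test: noncentrality δ√(n/2) = 0.64 × √6 = 1.57 and 0.64 × √5.5 = 1.50; power 32% and 30%.
- Adjusted for baseline: noncentrality about δ√(n/2)/√(1−ρ²) = 1.57/0.866 = 1.81 and 1.50/0.866 = 1.73; simulated power about 40% and 36%.

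**Step 4: both steps together.** The two tests share data, so this was simulated with 20,000 trials per scenario. Success is interaction p<0.05 and last-visit t-test p<0.05/m.

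| ρ = 0.5, Phase One / Phase Two | 0.64 SD | 1.28 SD |
|---|---|---|
| Gate, then Bonferroni over all visits | 9% / 6% | 64–65% / 50% |
| Gate, then Bonferroni over post-baseline visits | 11% / 7% | 70% / 54% |
| Gate, no Bonferroni | 15% / 11% | 77% / 64% |
| Unadjusted last-visit t-test | 32% / 30% | 85% / 82% |
| Interaction alone | 33% / 22% | 89% / 73% |
| Baseline-adjusted contrast | 40% / 36% | 92% / 89% |

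With no true effect (Phase Two), the adjusted contrast rejects in 4.9% of trials and the two-step route in 0.3%.

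**Step 5: sensitivity.**
- At 0.64 SD and ρ = 0.7, the two-step route gives 12%/8% and the adjusted contrast 54%/49%.
- At 1.28 SD and ρ = 0.3, the two-step route gives 57%/42%, the interaction 76%/57% and the adjusted contrast 87%/83%.
- With a flat Phase Two effect at ρ = 0.5, the interaction rises to 29% (0.64 SD) and 86–87% (1.28 SD), closer to the adjusted contrast.
- At ρ = 0.8 with a flat effect, the interaction is one to two points ahead of the adjusted contrast (Phase One, 0.64 SD: 70% against 68%).

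**The case against.** The strongest reply is that a greater reduction in pain is a difference in change over time, which is what the interaction tests. Post hoc comparisons only follow it up, and nothing says that benefit is declared only if a last-visit comparison also passes. This stands. The both-steps event is one possible reading of success. Against the interaction alone the loss is 33% to 40% in Phase One and 22% to 36% in Phase Two at 0.64 SD.

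Four stronger readings are tempting, and the documents do not support them:
- *Arms are compared only through the gate.* An ungated t-test with a 95% CI is also reported, and the ANOVA has its own arm effect. What remains is that the t-test is supplementary and unadjusted, and that the arm effect averages in the pre-intervention visit.
- *Bonferroni runs over all visits.* The family is not stated. With two arms there is one pair per visit, so a correction within a visit would leave 0.05 unchanged. The gate-only row covers that case and still shows a loss.
- *The route misses most real differences.* This is so at 0.64 SD, but there the plain t-test also misses about 70%, so much of the shortfall is sample size. At 1.28 SD the route succeeds in about half of trials or more at ρ = 0.5.
- *A plain last-visit t-test would be better than the plan's interaction test.* In Phase One it is not: 32% against 33% at ρ = 0.5, and 32% against 52% at ρ = 0.7. The gain needs baseline adjustment.

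An interaction followed by corrected comparisons is also conventional and conservative on type I error, and a separate analysis plan may define the family. That is a fair limit on the point, but the gate and the correction are stated in this document.

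**Conclusion.** The point holds in a limited form. The protocol leaves the primary BPI test unnamed and fixes a gated, corrected route to visit-level comparisons that is neither what the sample size was based on nor the most powerful use of the data. Measured by passing both steps, the loss against one baseline-adjusted contrast is large: 9%/6% against 40%/36% at 0.64 SD, and 64–65%/50% against 92%/89% at 1.28 SD. Measured against the interaction alone, it is modest in Phase One and larger in Phase Two.

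These figures rest on the assumed correlation, the assumed time course, the smaller completer numbers and, for the two-step row, an assumed Bonferroni family. The direction against the two-step route held in every scenario run. Against the interaction alone, the advantage disappears at high correlation with a flat effect. The matter deserves correction because a non-significant BPI result also moves the choice of Phase Two pressure to the next criterion.

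**What to change.** State that the primary test in each phase is one planned contrast: the between-arm difference in BPI at the end-of-treatment visit (day 5 in Phase One, day 15 in Phase Two), adjusted for baseline BPI. It may come from ANCOVA or from the equivalent contrast in the repeated-measures model. Test it at two-sided 5% and report it with its 95% CI whatever the interaction shows. Make the interaction and the other-visit comparisons secondary or descriptive, define any Bonferroni family, and leave the pre-intervention visit out of it. Say that this same contrast decides whether the pain difference is statistically significant in the step that selects the Phase Two pressure.

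The cost is a few sentences and no extra patients or data. The downside is that differences at interim visits, and at the Phase One day 6 follow-up, become descriptive. The change does not cure the small sample: at 0.64 SD the adjusted contrast still has only about 40% and 36% power at 12 and 11 per arm with ρ = 0.5.
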